**Materials and methods**

*Trial design*

This will be a multi-centre, parallel, single-blind, randomised superiority trial of CS-ADL versus TAU for people with mild-to-moderate dementia. Sample size was calculated using formal power analysis with G*Power software (Faul et al., 2007). Based on Cohen’s (1988) guidelines for small (*r =* 0.1), medium (*r* = 0.3) and large (*r =* 0.5) effects for a 2 (pre- and post-test) x 2 (CS-ADL and TAU) *t*-test, with the difference between two dependent means (matched pairs), sample size was calculated for an estimated small (*d =* 0.2), medium (*d* = 0.5) and large (*d* = 0.8) effect size. Two-tailed alpha of 0.05 was assumed for all tests. With an estimated effect size of 0.2, a sample size of 199 is required for a critical t of 1.9720175 and degrees of freedom (df) of 198, with an actual power of 0.8016910. With an estimated effect size of 0.5, a sample size of 34 is required for a critical t of 2.0345153 and a df of 33 and an actual power of 0.8077775. For an estimated effect size of 0.8, a sample size of 15 was calculated to be required for a critical t of 2.1447867 and a df of 14, with an actual power of 0.8213105. It is expected there will be challenges in the recruitment of 199 participant for the estimated effect size of 0.2, therefore for pragmatic reasons, recruitment will aim for the sample size of 34 (*d* = 0.5). Participants will be randomised with 1:1 allocation ratio to either the intervention or control group. The primary and secondary outcomes will be measured at baseline prior to randomisation and at the end of intervention (8 weeks). There will also be an observational assessment of occupational performance completed by the treating therapists within every group session.

*Study setting*

The study will take place in two Irish Health Service Executive (HSE), community-based occupational therapy services. The principal investigator will deliver the CS-ADL intervention.

*Eligibility criteria*

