The study sample will be analysed using descriptive statistics through the latest version of Statistical Package for Social Sciences (SPSS). Data on recruitment will be recorded and examined. A Consolidated Standards of Reporting Trials (CONSORT) diagram describing the flow of participants through the study will be presented in the final RCT report, detailing enrolment, allocation, follow-up, and analysis of data (Figure 1). Baseline data will be assessed for normality and if normally distributed, parametric analysis will be used. Where data is not normally distributed, non-parametric analysis will be used. Types of tests chosen will be based on whether the data is parametric or non-parametric. Significance levels will be set to 0.05. A linear regression model adjusting for baseline scores will be used to estimate the effect of intervention on each of the primary and secondary outcomes, with a between-group analysis completed to examine if the groups are significantly different at outcome. A within-group analysis will be also completed to evaluate if there are any significant changes within groups. Sociodemographic factors like age and gender will be entered as covariates.

*Ethical considerations*

The researchers are currently in the process of receiving ethical approval for this study.

*Anticipated risks for trial participants*

There appear to be no documented harmful side effects from participating in typical CS programs, with no adverse reactions apparent. Health and safety risks, including the risk of falls may be posed by the participation in cooking tasks and physical activities. However, group facilitators will use their clinical judgement, clinical risk assessments in the implementation of activities and always ensure adequate supervision is given. Nevertheless, potential participants and their caregivers will be fully informed of the potential risks before partaking in the trial.

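### Test choice is keyed to normality of baseline data, which is the wrong check, and the Protocol does not say whether its baseline-adjusted regression still governs when that check fails

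*Protocol*

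**What the plan says.** All the relevant text is in one paragraph of the Protocol, the Statistical analysis subsection.

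- The trigger: "Baseline data will be assessed for normality and if normally distributed, parametric analysis will be used".
- The fallback, with no test named: "Where data is not normally distributed, non-parametric analysis will be used".
- The scope: "Types of tests chosen will be based on whether the data is parametric or non-parametric".
- The effect estimate, stated without condition: "A linear regression model adjusting for baseline scores will be used to estimate the effect of intervention on each of the primary and secondary outcomes", and, in the same sentence, "with a between-group analysis completed to examine if the groups are significantly different at outcome".
- An additional analysis: "A within-group analysis will be also completed to evaluate if there are any significant changes within groups".

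The Trial design subsection gives the setting: 34 participants in total, 1:1 allocation, a target effect of d = 0.5, outcomes at baseline and week 8, and "Two-tailed alpha of 0.05 was assumed for all tests".

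**The concern.** There are two faults in what the paragraph fixes.

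First, the criterion is misplaced. Linear regression of the week-8 score on arm and baseline score assumes nothing about how the baseline score is distributed. What matters for its standard errors and p-values, particularly in a small trial, is how the residuals behave. A skewed baseline can go with well-behaved residuals, and a normal baseline with poor ones.

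Second, the two instructions collide. Linear regression is a parametric analysis. If baseline data fail the check, one sentence calls for non-parametric analysis and another calls for the regression on every outcome. The Protocol does not rank them, so the primary analysis is not settled in that case.

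At stake is precision. With 34 participants, baseline adjustment is a main source of power, and an unadjusted rank test gives it up. It would also give no adjusted mean difference.

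The planned within-arm significance tests add a smaller problem: a significant change in one arm does not address the Protocol's hypotheses, which compare CS-ADL with TAU.

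**Working it through.** **Inputs from the Protocol.** N = 34 at 1:1, so 17 per arm; d = 0.5; two-sided alpha 0.05.

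**Assumptions (the Protocol gives none of these).** The correlation r between baseline and week-8 score is 0.5, 0.7 or 0.8. The normality check is Shapiro-Wilk at 5%. The fallback is Mann-Whitney on week-8 scores. The skewed baseline is a reflected gamma. Here d = 0.5 is taken as the between-arm difference in SDs of the week-8 score; the Protocol uses it for a paired difference.

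**1. The Protocol's own figures.** For a paired t-test with df = n - 1 and noncentrality d x sqrt(n), n = 199, 34 and 15 give power 0.80169, 0.80778 and 0.82131, with critical t 1.97202, 2.03452 and 2.14479. All agree with Trial design. They describe a paired test, so they do not give the power of the between-arm regression.

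**2. Power of the adjusted regression.** Residual SD = sqrt(1 - r^2), df = 31, noncentrality = 0.5 / sqrt(1 - r^2) x sqrt(17/2).

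- r = 0.5: 0.5/0.866 x 2.915 = 1.68, power 0.37.
- r = 0.7: 0.5/0.714 x 2.915 = 2.04, power 0.51.
- r = 0.8: 0.5/0.600 x 2.915 = 2.43, power 0.65.

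**3. Large-sample efficiency of an unadjusted Mann-Whitney test against that regression, normal data.** About 0.955 x (1 - r^2): 0.72, 0.49 and 0.34 at the three values of r.

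**4. Is the check relevant?** Simulation used a skewed baseline (reflected gamma, shape 1.5), exactly normal regression errors and 6,000 trials per setting. Shapiro-Wilk rejected baseline normality in about 91% of trials. It rejected normality of the regression residuals in about 5%, the nominal rate. In this setting the rule abandons a valid model most of the time.

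**5. Cost if the rule displaces the regression (same simulation).**

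| r | Regression kept | Rule: Shapiro-Wilk, then regression or Mann-Whitney | Mann-Whitney on change |
|---|---|---|---|
| 0.5 | 0.369 | 0.290 | 0.287 |
| 0.7 | 0.494 | 0.316 | 0.422 |
| 0.8 | 0.642 | 0.346 | 0.590 |

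A rerun in which Shapiro-Wilk rejected baseline in about 82% of trials gave nearly the same answer: about 0.35/0.50/0.65 with the regression kept, and 0.28/0.33/0.36 under the rule. With milder skew (about 0.7) the rule triggered in about 28% of trials, and power at r = 0.7 fell from 0.49 to 0.43.

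**6. Where the cost disappears.** With a normal baseline and r = 0.7, power goes from 0.499 to 0.489, about 1 point. With errors skewed as well as baseline, Mann-Whitney on change scores is roughly level with the regression: 0.50 and 0.51 at r = 0.7, then 0.70 for the rank test against 0.66 for the regression at r = 0.8.

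**7. Type I error at r = 0.7, no effect.** Under the rule it is 0.050 with a normal baseline and 0.053 with a skewed one. Under the regression it is 0.051 in both.

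**The case against.** The strongest reply is that the regression sentence carries no condition. On that reading the regression always estimates the treatment effect, and the normality rule governs only the other comparisons, such as the within-arm tests. The Protocol names no rank test and nowhere says that adjustment is dropped. This stands in part: displacement of the regression is one reading of two unreconciled statements. But the scope sentence, "Types of tests chosen will be based on whether the data is parametric or non-parametric", makes no exception for the treatment comparison, so the opposite reading is equally open.

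A second reply is that the size of the loss comes from the reviewer's inputs. That also stands. The documents give no baseline distribution and no correlation, so how often the rule would trigger is unknown.

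Three stronger inferences are tempting but unsupported.

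- *The rule inflates false positives.* It is stated in advance and triggered by baseline data, and its simulated type I error stays near 5%.
- *The within-arm tests will be offered as proof of effect.* The Protocol's hypotheses are between-arm and a between-arm analysis is planned. How often CS-ADL alone would be significant when both arms change equally depends on the assumed change. At n = 17 per arm it is p(1 - p), where p is the power of the within-arm test: about 5% with no change, 11% at 0.2 SD and 25% at 0.5 SD. The documents support none of these values in particular.
- *The covariate list is left open.* The wording is "Sociodemographic factors like age and gender will be entered as covariates". Completing such a list is ordinary SAP work and is not counted here.

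**Conclusion.** The point holds in a limited form. Two things follow from the text alone: baseline normality is the wrong criterion for a baseline-adjusted regression, and the paragraph does not say which instruction prevails when that criterion fails. This is a stated rule that misdirects the analysis, not detail awaiting a SAP.

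The size is conditional. If the regression gives way to an unadjusted rank test on week-8 scores, and baseline is clearly skewed with normal errors, the loss is about 7, 17 and 29 percentage points of power at r = 0.5, 0.7 and 0.8 (0.35 - 0.28, 0.50 - 0.33, 0.65 - 0.36). It is about 1 point with a normal baseline, and smaller or absent at r = 0.7 and 0.8 if the rank test uses change scores. A reader might infer that the Protocol has definitely abandoned its adjusted analysis, or that its error rate is compromised. The documents support neither. The harm is an unsettled primary analysis and avoidable loss of power in a small trial.

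The within-arm tests are a secondary matter: they cannot answer the CS-ADL versus TAU question and should not carry p-values.

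**What to change.** - Delete the sentences that tie parametric or non-parametric analysis to baseline normality.
- State that the baseline-adjusted linear regression of the week-8 score is the single primary analysis for each outcome, whatever the baseline distribution, reported as an adjusted mean difference with a 95% confidence interval.
- State that residuals from this model will be checked. If they are poor, add a bootstrap or robust-standard-error interval for the same model as a sensitivity analysis.
- Report within-arm change descriptively, with a confidence interval and no significance test.

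The cost is a few sentences in the Protocol or SAP, plus a little extra analysis work if the sensitivity interval is needed.

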**Discussion**

Dementia is a progressive syndrome where deteriorating cognitive, behavioural, and emotional functions impede on the individual’s ability to engage in meaningful occupations and ADLs. Traditional discussion-based CS programs have not demonstrated consistent benefits for ADL outcomes for individuals with mild-to-moderate dementia. This has prompted the development of CS-ADL, an ADL-focused multi-component CS program, informed by the results of Ryan and Brady’s (2023) scoping review and a pilot study conducted within the Mullingar PLL services. A single-blind, parallel, randomised superiority trial has been proposed, aiming to evaluate the benefits of CS-ADL on the ADL outcomes of individuals living with mild-to-moderate dementia, in comparison to TAU. The proposed RCT also intends to evaluate the effects of CS-ADL on cognition, communication, QOL and mood of participants in comparison to TAU. To the extent of the authors knowledge, this study will be the first of its kind conducted within the Irish PLL services and will provide valuable evidence of the effectiveness and feasibility of implementation of a multi-component CS intervention in a community setting. This study aims to influence the approach to CS intervention undertaken by Irish occupational therapists working in community PLL services.

Funding: Funding for this trial will be sought from the Irish Research Council, Alzheimer's society of Ireland or the Health Research Board, Ireland. Funding will contribute to the provision of materials for the CS ADL sessions and the transport of participants to the study centre.

Contributors: [name] is the primary investigator for this study. [name] is the co-investigator of the study and is responsible for the original concept of the trial and for ensuring that the study follows the agreed protocol. [name], [name], staff grade occupational therapists, and [name] were involved in the design of the study’s group protocol and for piloting the intervention sessions. [name] were involved in the review and approval of the RCT protocol.

Appendix 1 CS-ADL Groupwork Protocol

| **CS-ADL Groupwork protocol** | |
| --- | --- |
| **Group title** | Cognitive stimulation in activities of daily living for individuals with mild-to-moderate dementia (CS-ADL) |
| **Author(s)** | [name], senior occupational therapist; lecturer in Occupational Therapy.  [name], occupational therapist and masters of philosophy (M.Phil) student in occupational therapy, University of Galway.  [name], staff grade occupational therapist.  [name], staff grade occupational therapist. |
| **How to reference:** | [name], [name], [name], [name] (2022) Cognitive stimulation in activities of daily living for individuals with mild-to-moderate dementia (CS-ADL). [Unpublished manuscript]. |
| **Purpose** | This group aims to provide benefits for the performance of activities of daily living (ADLs) for individuals with mild-to-moderate dementia. This group involves the delivery of cognitive stimulation through an occupational therapy lens; physical activity and ADL-based activities are incorporated into a program of cognitive stimulation, with the aim to improve/maintain ADL outcomes. |
| **Evidence-base** | Cognitive stimulation (CS) involves engagement in a range of activities and discussions with the aim to enhance cognitive and social functioning (Clare and Woods, 2004). However, a recent scoping review of the use of CS in ADLs for individuals with mild-to-moderate dementia reported that traditional, discussion-based CS approaches do not benefit ADL outcomes (Ryan and Dolan, 2022). In comparison, studies evaluating multi-component approaches to CS, incorporating physical activity and ADL-based activities into their program reported significant benefits for ADLs (Graessel et al., 2011; Jiménez Palomares et al., 2022). |
| **Frames of reference** | Activities will be based on a rehabilitative frame of reference (FoR). This FoR is typically used with individuals whose underlying difficulties are unlikely to be remediated and will therefore be used to inform this group as dementia is often of a progressive, degenerative nature (Gale et al., 2018). The rehabilitative FoR aims to maximise independence by utilising areas of strength rather than attempting to remediate areas of deficit. This will be achieved using cognitive stimulation strategies and ADL practice in conjunction with the instruction of compensatory methods like assistive equipment and memory aids. Members will also gain support from each other through group discussion and problem-solving of everyday scenarios. |
| **Logistics** | *Place of meeting:* Occupational therapy services. Group room to have adequate table and seating arrangements.  *Number of clients:* A closed group of approximately 5-10 individuals.  *Group facilitators:* The group will be facilitated by at least one qualified occupational therapist. Co-facilitation can be by fellow occupational therapist, healthcare assistant, student or relevant health and social care professional.  *Schedule:* The program will span 7 weeks, consisting of once weekly sessions lasting approximately 2 hours.  *Advertisement/promotion:* The group will be promoted to fellow clinicians within local services, who will screen their caseload for potential participants. |
| **Group structure** | Each session consists of similar components, however the sequence and timing allocated per component may occasionally differ between sessions. An example of the session structure is detailed below:  Sessions will begin with introductions, reality orientation, a group song, and a discussion of news of the week. This will be followed by warm-up exercises before a physical activity/game. ADL-focused cognitive stimulation activities will be completed before a 15-minute break, after which the main ADL-based activity will be completed. Sessions will be concluded with a group song. A full breakdown and method of each session is detailed below. |
| **Group goals** | This group aims to:  -Provide opportunity for participants to receive peer support for memory and thinking challenges and/or the experiences of later life through a group environment.  -Provide a supportive environment in which participants with communication difficulties can express themselves amongst their peers.  -Provide benefits for cognition including improving the arousal levels of participants.  -Provide health benefits of exercise for participants through engagement in low-impact physical activity.  -Benefit mood of participants through opportunities to engage in physical activity, socialisation, and meaningful occupations.  -Provide an environment where participants are actively engaged and involved in the planning, preparation, and practice of ADLs.  -Increase participants confidence in the performance of ADLs.  -Introduce compensatory approaches to ADLs, providing opportunities for participants to explore compensatory devices and techniques of interest to them. |
| **Essential requirements for group membership** | -Older adults with a diagnosis of major neurocognitive disorder as per the DSM-V criteria (American Psychiatric Association, 2013).  -Group members must have a mild-to-moderate cognitive impairment, as assessed by the MoCA, or MoCA-Blind administered over the telephone. Individuals with severe cognitive impairment will not be suitable for group membership.  -Group members must have some ability to communicate and understand communication, determined by a score of 1 or 0 on questions 12 and 13 of the Clifton Assessment Procedures for the Elderly-Behaviour Rating Scale (Pattie and Gilleard, 1979).  -Individuals with significant uncontrolled disruptive behaviours, a premorbid diagnosis of learning disability, or a significant physical illness/disability that affects participation during intervention sessions will not be suitable for group membership. |
| **Outcome measures** | Primary outcomes of the group will be basic ADL (BADL) and instrumental ADL (IADL) outcomes.  -The Alzheimer’s Disease Co-operative Study – Activities of Daily Living (ADCS-ADL) will be used to measure BADL and IADL outcomes.  Secondary outcomes will be cognition, communication, mood, and quality of life.  -Cognition is a secondary outcome of this group and general cognitive functioning will be measured using the Montreal Cognitive Assessment (MoCA) or MoCA-Blind via telephone, dependent on feasibility for participants or the assessor. Cognitive functioning will be assessed using the Repeatable Battery for Assessment of Neuropsychological Status (RBANS). This battery assesses five cognitive domains: immediate memory, visuospatial-constructional ability, language and delayed memory.  -Communication ability will be measured using the Holden Communication Scale (HCS).  -Quality of life will be assessed using the Quality of Life-Alzheimer’s Disease Scale (QOL-AD).  -Mood will be assessed through the presence of neuropsychiatric symptoms as measured by the neuropsychiatric inventory questionnaire (NPI-Q). |
| **Referral criteria** | Please refer to eligibility criteria. Local occupational therapy referral protocols to be followed. |

Appendix 2.1 CS-ADL individual session plans

| **Session Number:** | 1 of 7 |
| --- | --- |
| **Group Title:** | Cognitive stimulation in activities of daily living for individuals with mild-to-moderate dementia (CS-ADL) |
| **Session Theme:** | Morning routine |
| **Preparation:** | |
| *Set-up* | Arrange adequate seats around a table in the centre of the room. Place a newspaper on the table. Ensure a whiteboard/flipchart and a clock are set up and visible in the room. Set up a separate cooking station near an outlet with hotplates available on the table (if a hob is not already available in the room). Ensure all other materials necessary are available in the room. |
| *Materials* | Whiteboard/flipchart, marker, newspaper, inflatable ball, fly swatters and balloon, 8 drawstring bags, 2-4 cardboard boxes, assortment of cleaning, cooking, and grooming equipment e.g., deodorant, toothpaste, salt and pepper shakers. Laminated instruction cards: ‘getting ready for the day’, ‘cleaning’, ‘breakfast’. Array of assistive devices e.g., button hook, shoehorn, pillbox. Chopping boards, knives and forks, hotplates, frying pans, spatula, take-away plates, and tinfoil. Breakfast foods e.g., eggs, sausages, bacon, tomatoes. |
| **Format:** | |
| *Introduction* (20 minutes) | Greetings.  Warm-up activity: Pass inflatable ball/balloon around the group. Instructions provided to introduce self while holding the ball and to tell the group about themselves.  Group provides suggestions of potential group names and a song that will be sung at the beginning of each session. (If necessary, group facilitators should have a variety of options for group members to choose from). Group name to be written on whiteboard/flipchart.  Orientation of day of the week, date, month, year, season, and time to be discussed and written on whiteboard.  Discussion of news of the week. |
| *Physical activity* (15 minutes) | Gentle seated stretches to warm-up.  Seated physical activity to involve a team balloon game. This game involves keeping a balloon up in the air and off the floor by using fly swatters. Group members should be split into two teams and seated opposite to each other. Group members should work in their teams to try and pass the balloon to a goal without letting the balloon fall to the ground. Group facilitators can act as the ‘goal’. |
| *Cognitive stimulation activities* (30 minutes) | Perception-based activities: group members asked to place their hand into a bag without looking and identify everyday items relating to morning routine through touch alone. Prompting questions to be provided by group facilitators, members to verbally describe what they would do with the item.  Group members to break off into smaller groups if possible. Members to rummage through cardboard boxes filled with an assortment of cleaning, cooking and grooming items related to the theme of morning routine. Members to sort items in the box into categories by placing them on laminated instruction cards of ‘cleaning’, ‘breakfast’, and ‘getting ready for the day’ (appendix 2.2). Members encouraged to discuss, and problem solve together.  An array of assistive devices related to the theme of morning routine to be placed in a bag e.g., shoehorn, button hook, jar opener, pillbox. Group members to pull out an item from the bag and guess its purpose. Use of assistive devices to be demonstrated by group facilitators with practice of use by group members. |
| *Break* (15 minutes) | Tea/coffee and biscuits to be provided to group members. Group facilitators to encourage casual conversation amongst members. |
| *Cognitive stimulation activities* (10 minutes) | Discussion and sequencing of morning routine amongst group members: getting ready for the day, breakfast routine. Discussion and reminiscence of various breakfast recipes. |
| *ADL practice* (30 minutes) | Group members to split into smaller groups and asked to prepare and cook a fried breakfast from a range of ingredients, using the hob and pans. Recipe discussion and reminiscence to be encouraged throughout by group facilitators. Food to be served up onto take-away plate to take home. |
| *Conclusion* (5 minutes) | Group facilitators to summarise session and ask for feedback. Group to sing group song. Facilitators to remind everyone of next session. |
| **Rationale for activities chosen:**  A physical game was chosen as the first activity to build rapport amongst members and facilitate socialisation within the group. Physical activity was also a component of a variety of CS approaches reviewed by Ryan and Dolan (2022), with 7 of 9 studies involving a physical activity component to intervention reporting benefits for ADL outcomes.  Chosen activities aim to target a variety of cognitive domains. Targeted domains of this group are reflective of previous CS programmes reported to have ADL benefits (Jiménez Palomares et al., 2022; Muñiz et al., 2015). Orientation is targeted through identifying day, date, month etc. and through discussion of ADLs in relation to time and location. Attention and verbal language/fluency is targeted consistently throughout the session. Memory and perception are targeted in the tasks required to identify and categorise everyday items. Praxis and perceptual-motor abilities are targeted through the physical activity and ADL practice, with executive function skills used to sequence and plan ADL-related activities.  Completion of an ADL task is an essential component of the group, as Ryan and Dolan’s (2022) scoping review indicated CS interventions with an ADL component report benefits for ADL outcomes. | |
| **Session Number:** | 2 of 7 |
| **Group Title:** | Cognitive stimulation in activities of daily living for individuals with mild-to-moderate dementia |
| **Session Theme:** | Afternoon routine |
| **Preparation:** | |
| *Set-up* | Arrange adequate seats around a table in the centre of the room. Ensure a newspaper is available on the table. Ensure a whiteboard/flipchart and a clock are set up and visible in the room. Ensure all other materials necessary are available in the room. Set up electric bed if required with adequate space for demonstration. |
| *Materials* | Whiteboard/flipchart, marker, newspaper, inflatable ball, laminated print out of group song, plastic cups, small ball/tennis ball, electric bed, assistive devices for the bedroom e.g., bed lever, non-slip dycem mats etc. ‘How to get up from a fall’ laminated handouts. Washing basket full of an assortment of clothes, mannequins, pen and paper, whiteboards/corkboards, small plant pots, seed packets, gardening tools, soil. |
| **Format:** | |
| *Introduction* (20 minutes) | Greetings.  Warm-up activity: Pass inflatable ball/balloon around the group. Instructions provided to introduce self while holding the ball and to tell the group about their favourite time of year.  Group asked to recall group name and song chosen last week. Laminated song sheets to be handed out to group members to sing together.  Orientation of day of the week, date, month, year, season, and time to be discussed and written on whiteboard.  Discussion of news of the week. |
| *Physical activity* (15 minutes) | Gentle seated stretches to warm-up.  Physical activity to involve a game of bowling. Split group members into smaller groups and ask them to stack plastic cups into a pyramid. Group members to then take turns bowling a tennis bowl into the cups, and re-stacking when needed. |
| *Cognitive stimulation activities* (30 minutes) | Follow up from previous session with a continued discussion and reminiscence of morning routines, e.g., do you make the bed, do you like making the bed, how do you get in and out of bed etc. Discussion of tips on making the bed and demonstration of the use of assistive devices in relation to getting in and out of bed e.g., bed lever, coloured sheets, non-slip dycem mat. Group facilitators to demonstrate use of the electric bed and to provide opportunity for group members to practice use.  Group facilitators to discuss and demonstrate how to get up from a fall out of bed, providing handouts (appendix 2.3).  An assortment of clothes is to be placed on the table. Group members are to identify and discuss different types of clothes from the pile that they would wear for different occasions. Members then asked to work together to dress mannequins for certain occasions, for example, going to the beach or for a rainy day. |
| *Break* (15 minutes) | Tea/coffee and biscuits to be provided to group members. Group facilitators to encourage casual conversation amongst members. |
| *Cognitive stimulation activities* (15 minutes) | Continued discussion of afternoon routine, discussion of going out for the day, what group members need to bring with them when leaving the house. Discussion of to do lists and reminders. Group members to practice writing down what they need when leaving the house as a reminder. Group facilitators to type these lists up later and provide a printed and laminated version to group members at the next session. Whiteboards/corkboards to be introduced and group to discuss their purpose. |
| *ADL practice* (20 minutes) | Simple gardening activity: group members to be provided with small pots, gardening tools, a variety of seed packets and a bag of soil. Facilitators to assist members in gardening task. Discussion to be encouraged throughout activity. |
| *Conclusion* (5 minutes) | Group facilitators to summarise session and ask for feedback. Group to sing group song. Facilitators to remind everyone of next session. |
| **Rationale for activities chosen:**  All sessions include the components of cognitive stimulation, physical activity, and ADL practice. This session targeted the cognitive domains of orientation through the identification day, date, month etc., and through the discussion of ADLs in relation to time and location. Attention and verbal language/fluency are targeted consistently throughout the session. Memory and perception are targeted through the dressing activity requiring the identification and categorisation of everyday items. Praxis and perceptual-motor abilities are targeted through the physical activity and ADL practice, with executive function skills used in the sequencing and planning of ADL-based activities. Furthermore, written language is targeted through the completion of writing tasks. | |
| **Session Number:** | 3 of 7 |
| **Group Title:** | Cognitive stimulation in activities of daily living for individuals with mild-to-moderate dementia |
| **Session Theme:** | Domestic activities 1 |
| **Preparation:** | |
| *Set-up* | Arrange adequate seats around a table in the centre of the room. Ensure a newspaper is available on the table. Ensure a whiteboard/flipchart and a clock are set up and visible in the room. Set up a clothesline with a table and chairs nearby. Ensure all other materials necessary are available in the room. |
| *Materials* | Whiteboard/flipchart, marker, newspaper, inflatable ball/balloon, cue cards for physical activity, laminated print out of group song, music player, pen and paper, clothesline, clothes pegs, laminated instructions sheets for clothesline activity, washing basket, ironing board, iron, various domestic items e.g., washing up liquid, shoe polish and brush, colour catchers etc. Assortment of clothes and socks, variety of scented items e.g., baby powder, flowers, polish etc. Cotton pads/tissues. |
| **Format:** | |
| *Introduction* (20 minutes) | Greetings.  Warm-up activity: Pass inflatable ball/balloon around the group. Instructions provided to introduce self while holding the ball and to tell the group about their favourite holiday destination.  Group asked to recall group name and song. Laminated song sheets to be handed out to group members to sing together.  Orientation of day of the week, date, month, year, season, and time to be discussed and written on whiteboard.  Discussion of news of the week. |
| *Physical activity* (15 minutes) | Gentle seated stretches to warm-up.  Physical activity: Prepare cue cards with questions written on the back. Then take a soft ball or balloon and throw it towards a person in the group. Pick a cue card and ask the question. The person who catches the ball answers the questions. Take turns until all questions have been answered. |
| *Cognitive stimulation activities* (30 minutes) | Discussion and reminiscence of household chores, e.g., what chores do you do around the house, do you like doing these activities, what chores did you do when you were younger. Group members asked to describe and sequence domestic tasks like doing the laundry, with some members asked to write out step-by-step instructions.  A variety of household items are placed on the table e.g., shoes and shoe polish, washing up liquid, sponge, gloves, cleaning products, cloths etc. Group members are asked to discuss and demonstrate the use of these items and pair items that would be used together.  Group members to be split into smaller groups if appropriate (dependent on group size). One group to take part in a clothesline activity, the other group to take part in a matching activity. Groups will then be rotated.  Matching activity: unpaired socks are to be hidden in a pile of clothes and group members will be asked to find the socks and pair them.  Clothesline activity: laminated instruction cards stating, ‘1 pair of blue socks’, ‘3 shirts’, or a ‘red jumper’, to be used in this task (appendix 2.4). Group members asked to pick a card, read out the instruction and search for the items in the pile of clothes. Items are then to be hung up on the clothesline. Group members encouraged to work together. |
| *Break* (15 minutes) | Tea/coffee and biscuits to be provided to group members. Group facilitators to encourage casual conversation amongst members. |
| *Cognitive stimulation activities* (20 minutes) | Sensory activity: a variety of different household scents e.g., baby powder, flowers, shoe polish, washing up liquid, should be placed on cotton pads and group members are asked to identify the smells.  Discussion of evening routine e.g., what do you have for dinner, when do you have dinner. Group members to decide on a dinner to make together for next weeks session, with members writing out a menu. Group facilitators to type up, print and laminate the menu, to be used in the next session. |
| *ADL practice* (15 minutes) | Preparation of a sandwich: group members provided with a variety of sandwich ingredients and asked to prepare a sandwich of their preference. Discussion of lunch preferences to be encouraged by group facilitators. |
| *Conclusion* (5 minutes) | Group facilitators to summarise session and ask for feedback. Group to sing group song. Facilitators to remind everyone of next session. |
| **Rationale for activities chosen:**  All sessions include the components of cognitive stimulation, physical activity, and ADL practice. This session targeted the cognitive domains of orientation through the identification day, date, month etc., and through the discussion of ADLs in relation to time and location. Attention and verbal language/fluency are targeted consistently throughout the session. Memory and perception are targeted through activities requiring the identification and categorisation of everyday items/scents. Praxis and perceptual-motor abilities are targeted through the physical activity and ADL practice, with executive function skills used in the sequencing and planning of ADL-based activities. Furthermore, this task targets the domain of written language/reading and numerical capacity, through the clothesline activity. | |
| **Session Number:** | 4 of 7 |
| **Group Title:** | Cognitive stimulation in activities of daily living for individuals with mild-to-moderate dementia |
| **Session Theme:** | Evening routine |
| **Preparation:** | |
| *Set-up* | Arrange adequate seats around a table in the centre of the room. Ensure hand sanitiser and facemasks are available on the table in accordance with COVID-19 preventative measures. Ensure a newspaper is available on the table. Ensure a whiteboard/flipchart and a clock are set up and visible in the room. Set up a separate cooking station near an outlet with hotplates on the table (if a hob is not already available in the room). Ensure all other materials necessary are available in the room. |
| *Materials* | Whiteboard/flipchart, marker, newspaper, inflatable ball, laminated print out of group song, tennis ball/small ball, targets, laminated copy of dinner menu, cardboard boxes, assortment of kitchen utensils, chopping board, frying pan, tongs, peelers, knives, hotplates, dinner ingredients e.g., potatoes, carrots, pork chops, oil. An assortment of non-kitchen related items e.g., toothpaste, deodorant, hairbrush, clothes etc. Laminated charades instruction cards, tin foil, take-away plates, variety of assistive technology relating to evening routine e.g., one button radio, easy to use TV remote, informational handouts. |
| **Format:** | |
